## Abstract

**Introduction:**

Fewer than half of patients receive evidence-based upper limb rehabilitation after stroke. Implementation science interventions may improve use of guidelines by clinicians; however, it is not yet known whether they lead to evidence-based stroke rehabilitation practice. We aim to determine the effect and cost-effectiveness of a champion-led implementation package (PROMOTE) to increase adherence to best practice guidelines for upper limb rehabilitation after stroke.

**Methods and analysis:**

A multistate, multicentre, cluster-randomised, implementation phase IV trial with concealed allocation, blinded measurement and intention-to-treat analysis will be conducted. The PROMOTE package includes appointing an internal champion, local audit and feedback, interactive education tailored to gaps in knowledge and skill, and a decision-aid to support intervention selection. To be eligible, centres delivered rehabilitation to at least 20 stroke patients in the preceding year. Assuming 35% baseline adherence to guidelines, 14 centres (n=238) will be recruited to provide 80% power to detect a 30% absolute difference with a two-sided α=0.05. An embedded process evaluation and economic analysis will assess implementation and costs. The primary outcome is the proportion of people with stroke who are documented to receive guideline-recommended upper limb rehabilitation interventions by 6 months. Secondary outcomes include self-reported clinician behaviour change, upper limb therapy outcomes at the end of intervention, costs and cost effectiveness (eg, incremental cost per quality adjusted life year). Process evaluation outcomes include reach, adoption, implementation and maintenance (sustainability).

**Ethics and dissemination:**

Ethical approval was obtained from the Alfred Hospital Human Research Ethics Committee (approval number 89725 (NMA), 26 April 2023) with each participating site providing ethical clearance prior to the commencement of the trial. Findings will be reported in accordance with the Consolidated Standards of Reporting Trials extended for cluster-randomised trials and in peer-reviewed journals, and communicated to stakeholders and the public. Understanding and characterising the active ingredients of effective implementation will inform scalable strategies to improve stroke rehabilitation practice, health outcomes and the equitable delivery of evidence-based care.

**Trial registration number:**

The trial is currently recruiting and is registered at https://www.anzctr.org.au/.

ID: ANZCTR 12623000608662 (UTN U1111-1292-8705), 2 June 2023.

STRENGTHS AND LIMITATIONS OF THIS STUDYThis is a fully powered, cluster-randomised phase IV implementation trial; randomising at the centre level, with matched pairing of centres and concealed, centrally-administered allocation, which protects against selection bias and minimises the risk of contamination between arms, although clinician movement between trial centres will be documented and accounted for in the analysis.While the design includes a cost-effectiveness analysis, embedded process evaluation and examination of post-implementation clinical outcomes, it does not assess sustainability of practice change after withdrawal of the champion and trial resources beyond the 6-month post-implementation phase.Centres vary in staffing, caseload, funding model and baseline guideline adherence; although matched-pair randomisation and pre-specified covariate adjustment will reduce confounding, residual centre-level heterogeneity may still influence implementation outcomes.The primary outcome relies on medical record audit and may be subject to documentation bias, although blinded assessors and standardised operational definitions will minimise this risk.All participating centres are within the Australian healthcare system and eligibility requires ≥20 stroke patients to be admitted per year; results may therefore not directly generalise to smaller, rural or resource-constrained services, to non-English speaking contexts or to healthcare systems with different funding models or staffing structures.

## Introduction

 There are over 440 000 Australians living with stroke,^1^ and approximately two-thirds experience upper limb impairments^2^ that affect their ability to perform everyday activities such as eating, dressing and washing.^3
4^ Upper limb impairments after stroke include not only muscle weakness but also reduced coordination and dexterity, compromising long-term independence.^5
6^ There is compelling evidence that delivering intensive, evidence-based upper limb rehabilitation will improve recovery,^7
8^ with guidelines recommending the amount and type of therapy (including constraint-induced movement therapy, repetitive task-specific motor training and electrical stimulation for strengthening).^9–17^

People with stroke who receive at least 2 hours a day^18^ of evidence-based upper limb rehabilitation^15
19^ are more likely to recover use of their arm. However, an Australia-wide audit of 103 rehabilitation services in 2024 showed that clinicians are not providing the recommended rehabilitation.^20^ Findings showed that services neither routinely provide the amount of upper limb rehabilitation recommended nor the most effective type of training, with little out-of-session practice. Importantly, the extent of this evidence-practice gap is not uniform: access to and receipt of rehabilitation by patients varies according to clinical factors such as stroke severity and upper limb impairment level, as well as socioeconomic and geographic factors, including rurality and healthcare system capacity.^21^ This multidimensional variation in rehabilitation access and delivery underscores the complexity of implementing guidelines at scale and highlights that effective implementation strategies must be responsive to the characteristics of clinicians, the healthcare recipients and the healthcare pathway. Similar challenges in translating guidelines into routine care have been observed in other areas of practice,^22
23^ reinforcing the importance of implementation interventions that are tailored to local context rather than applied uniformly.^24^

Existing implementation strategies in stroke rehabilitation, including audit-and-feedback approaches, have shown modest effects on clinician behaviour.^24^ However, audit and feedback alone is likely insufficient to drive sustained practice change when barriers to guideline uptake are multifactorial, encompassing gaps in the knowledge and skills of clinicians, limited access to resources, and cultural or organisational factors.^23
25^ What has been absent from the literature is a multicomponent, champion-led implementation package that combines education, skill-building, resourcing and feedback, tailored to the specific barriers identified at each centre, and tested in an adequately powered trial. Our Cochrane review confirmed this evidence gap,^24^ finding insufficient evidence to guide which strategies best support clinicians to deliver evidence-based neurorehabilitation.

Our pilot trial^26^ suggests that providing a champion to implement tailored support, including education and resources, improved guideline adoption. We additionally sought insights from clinicians and people with lived experience of stroke about the barriers and motivators for implementing upper limb rehabilitation guidelines,^27
28^ and tested methods of audit and feedback in rehabilitation.^29^ The pilot was a three-armed study testing: (1) PROMOTE+usual care versus (2) self-directed online resources+usual care versus (3) usual care alone. While we found that the champion-led package had a large effect, the self-directed package led to no greater increase in adherence than usual care. This suggests that passive dissemination, even when structured, was insufficient to drive practice change and that the active, champion-led components of PROMOTE were the likely drivers. Therefore, a larger adequately-powered trial is warranted to establish the effectiveness, cost-effectiveness and implementation characteristics of the full behaviour change package.

### Objectives

The primary objective is to evaluate the effectiveness of a champion-led implementation package versus usual standard rehabilitation on adherence to guideline recommendations for upper limb stroke rehabilitation in Australian hospitals.

Secondary objectives are:

To evaluate the effectiveness of a champion-led implementation package versus usual standard rehabilitation on clinician implementation behaviour, upper limb ability, health benefits and harms.To evaluate the economic cost of implementing the package.To assess the fidelity of delivery of the package.To understand use of the package in terms of reach, adoption, implementation and maintenance.

## Methods

This protocol was developed and reported in accordance with the Standard Protocol Items: Recommendations for Interventional Trials (SPIRIT) 2025 statement. The PROMOTE intervention was co-developed with key stakeholders, including adults living with stroke, clinicians working in upper limb rehabilitation and partners from the Stroke Foundation. Practical guidance on intervention design and delivery was informed by qualitative work with stroke survivors and clinicians,^27
28^ and by ongoing input from a stakeholder advisory group chaired by [name] (stroke survivor) and clinician stakeholder team members to ensure feasibility and real-world relevance.

### Design

The PROMOTE trial is a two-arm, cluster-randomised, phase IV trial^30^ with concealed allocation, blinded measurement and intention-to-treat analysis (figure 1). The risk of contamination between intervention and control centres is minimised by the cluster-randomised design, whereby randomisation occurs at the centre level; however, in the event that staff move between an intervention and a control centre during the trial period, this will be documented and considered in the analysis. Randomisation will be undertaken centrally by an independent statistician to ensure allocation concealment, both clusters within each matched pair will be enrolled and complete baseline assessment before allocation to minimise selection bias, and the randomisation schedule will be concealed until immediately prior to the implementation phase to maintain temporal concealment. The trial includes three phases: a baseline usual care phase (12 months); a randomised implementation phase (6 months) during which implementation outcomes are assessed; and a post-implementation usual care phase (6 months) during which clinical outcomes are assessed. Only data from the baseline and implementation phases will be used for the primary analysis. Given the nature of the primary outcome, minimal amount of missing data are anticipated. Subject to the satisfiability of missingness at random assumption, depending on the amount of missing data, either complete case analysis or analysis with multiple imputations with chained equations will be undertaken followed by the sensitivity analysis investigating the plausibility of missingness at random assumption. The details will be reported in the statistical analysis plan finalised prior to the study data lock. During the post-implementation period, patients with stroke will be sequentially recruited at each centre and patient measures will be collected at hospital admission and after 4 weeks of rehabilitation (or at the end of rehabilitation if discharged sooner). Economic outcomes will be measured continuously over the randomised implementation phase. Service delivery costs will be obtained from the centres for each trial phase (ie, to determine the implementation delivery costs).

**Figure 1 F1:**
[figure not shown]
Trial flow diagram demonstrating the cluster-randomised design with a baseline usual care period. Participating centres are randomised in pairs according to readiness to commence. mo, months.

### Participants, interventions and outcomes

#### Setting

Inpatient rehabilitation centres that deliver upper limb rehabilitation will be eligible to participate if they (1) employ at least one occupational therapist and/or physiotherapist, (2) receive >20 stroke referrals annually, and (3) have a level of adherence to guidelines <50% per stroke survivor in the previous Stroke Foundation rehabilitation services audit.^20^ Centres will be described by location, hours of therapy per bed (intensity of rehabilitation), funding (private vs public), staffing and caseload volume, and Australasian Rehabilitation Outcomes Centre data (eg, Functional Independence Measure (FIM) efficiency).

#### Eligibility criteria

Clinician participants will be occupational therapists and/or physiotherapists who work on participating wards and prescribe and deliver upper limb rehabilitation. Inpatients with stroke undergoing upper limb rehabilitation will be eligible to participate during the post-implementation phase if they are over 18 years old, have sustained a stroke in the previous 6 months, are able to read and understand spoken English to a level where they can understand the participant information sheet, can complete the consent form with/without an interpreter or next of kin, and have stroke-related difficulty using their upper limb that warrants rehabilitation (ie, have a minimum of 5° active finger or wrist extension and a maximum ability of 30 blocks/min on the Box and Block test).

#### Outcomes

The primary outcome is the proportion of inpatients with stroke with upper limb impairment who are documented to receive the recommended amount and type of upper limb rehabilitation during their admission. Guideline-recommended care was defined per the Stroke Foundation’s Clinical Guidelines for Stroke Management^11^ as ≥2 hours/day of active upper limb practice^18^ delivered using at least one of the constraint-induced movement therapy, repetitive task-specific training or electrical stimulation for strengthening; operational definitions for each are provided in online supplemental file D.

Secondary outcomes include change in clinician implementation behaviour as measured on a Theoretical Domains Framework questionnaire^38^ collected during baseline and implementation phases. Secondary clinical outcomes will be collected during the post-implementation phase, including change in upper limb ability (end of treatment minus admission) measured using the Box and Block test^39^ and Action Research Arm test.^40^ Health benefits will be estimated using the self-rated quality of life tool, EuroQol 5-Dimensions (EQ-5D-5L)^41^ and a preference-based single index score, using Australian preference weights, will be derived.^42^

Activity-based costing will be used to quantify the economic cost of implementing the interventions as an average cost per patient, inclusive of training, supervision and overall rehabilitation costs for eligible patients. Patient-level costs will be measured in $A and reported from a single reference year based on a societal perspective (including direct and indirect costs). Incremental cost per quality-adjusted life year gained will be estimated from the EQ-5D-5L data (change baseline to 4 weeks) and the total costs of intervention delivery compared across groups. Economic modelling will be used where relevant.

A process evaluation will be undertaken to collect intervention data and understand the use of the PROMOTE package within experimental centres from the perspective of clinicians, managers and people with lived experience. Deductive coding of transcribed interviews will be analysed alongside intervention data and findings will be reported according to the RE-AIM framework (Reach, Effectiveness, Adoption, Implementation and Maintenance).^43^

Because this phase IV trial implements only guideline-recommended interventions already expected to be delivered as part of routine care, the risk of study-related harm is low. Harms were defined a priori as any adverse events or unintended consequences occurring during usual rehabilitation and anticipated to potentially include falls, soft tissue injuries or unexpected deterioration in neurological or medical status. Assessment of harms will be the responsibility of the treating clinicians and will be logged and reported in accordance with institutional and ethics requirements.

#### Sample size

With a baseline adherence to guidelines of 35%,^44^ assuming control centres will increase this adherence to 40% and experimental centres to 70%, that is, an absolute difference of 30%, we will recruit 14 centres (clusters) evenly split between experimental and control arms. The intraclass correlation coefficient (ICC) observed in our pilot was <0.01.^26^ Assuming more conservative settings of ICC=0.05, a coefficient of variation of cluster sizes of 0.99 and no correlation between baseline measures and the outcome, recruiting 7 clusters per arm with an average 17 patients per cluster (a total sample size of 238 patients, 119 per arm) would yield power of 0.8 to observe an absolute difference of at least 30% with a two-sided alpha=0.05.

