#### Statistical analyses

Intention-to-treat analyses will be conducted. A statistical analysis plan will be finalised prior to locking the study database. For the primary analysis of the binary outcome of whether guideline recommendations were received by the participant or not, a three-level mixed effect logistic regression model with the intervention as independent variable and individual centre and the matched pair of centres used for randomisation as nested random effects will be used. The model will be adjusted for the following pre-specified covariates: baseline participant’s age and FIM score, as well as the cluster case volume and proportion of cases with guideline-recommended care provided during the baseline usual care stage. The intervention effect will be presented as adjusted odds ratio and standardised risk difference with respective 95% CI as per US Food and Drug Administration Guidance for Industry ‘Adjusting for Covariates in Randomized Clinical Trials for Drugs and Biological Products’. Relevant secondary outcomes will be analysed by appropriate mixed-effect regression models with the random effects specified as per the primary analysis adjusted for baseline participant’s age and baseline value of the respective outcome variable.

The economic evaluation will be conducted in accordance with the Consolidated Health Economic Evaluation Reporting Guidelines. The incremental cost-effectiveness ratio (ICER) will be calculated relative to the control group and will be reported as a cost per quality-adjusted life year gained. An ICER below $A 50 000 will be considered cost-effective. Acceptability curves of the probability that an intervention is cost-effective as a function of willingness to pay will also be plotted. Appropriate one-way sensitivity and multivariable uncertainty analyses or modelling will be performed to assess the robustness of results.

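### The stated power of 0.80 is that of an unmatched, unadjusted comparison; on the same assumptions the planned adjusted model has about 0.74 (0.71 to 0.77)

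*Protocol article*

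**What the plan says.** **Power.** The Sample size section assumes 40% adherence in control centres and 70% in experimental centres, 7 centres per arm, a mean of 17 patients per centre, an ICC of 0.05, a coefficient of variation of cluster size of 0.99, and zero correlation of baseline measures with the outcome. It concludes that this "would yield power of 0.8 to observe an absolute difference of at least 30% with a two-sided alpha=0.05". It calls these settings conservative and reports a pilot ICC below 0.01. The Abstract repeats the figure: "14 centres (n=238) will be recruited to provide 80% power to detect a 30% absolute difference". The strengths and limitations list describes a "fully powered, cluster-randomised phase IV implementation trial".

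**Design and analysis.** Under Randomisation and blinding, centres are randomised 1:1 within pairs matched on throughput, reported guideline adherence and metropolitan or rural location. Under Statistical analyses, the primary model is a three-level mixed logistic regression with "individual centre and the matched pair of centres used for randomisation as nested random effects will be used". It adjusts for two patient-level covariates, FIM and age, "as well as the cluster case volume and proportion of cases with guideline-recommended care provided during the baseline usual care stage".

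The Sample size section mentions neither the pairing nor the adjustment. Only its zero-correlation assumption touches on them.

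**The concern.** Both the power figure and the primary model are fixed in this document, and they do not belong to the same analysis. With only 14 centres, two centre-level covariates are a real charge on the arm contrast: they use up centre-level information, and chance imbalance in them between arms inflates the standard error. The return is lower between-centre variance, but the Sample size section sets that return to zero for baseline measures. The document therefore cannot draw on it to support its own 0.80.

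At stake is the reading of a non-significant result. On the stated assumptions, the chance of missing a true 30-point difference would be about 23% to 29%, not 20%, under a headline that says 80%.

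**Working it through.** **Step 1: reproduce the stated figure** (all inputs from the Sample size section).

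- Design effect = 1 + [(1 + CV²) × m − 1] × ICC = 1 + [(1 + 0.99²) × 17 − 1] × 0.05 = 2.633
- Effective patients per arm = 119 / 2.633 = 45.2
- Standard error = √[(0.40 × 0.60 + 0.70 × 0.30) / 45.2] = √(0.45 / 45.2) = 0.0998
- Non-centrality = 0.30 / 0.0998 = 3.006
- Power, noncentral t, 14 − 2 = 12 df: **0.788**
- Power, normal approximation: 0.829 (pooled variance) or 0.852 (unpooled)

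The arithmetic is sound for an unmatched, unadjusted comparison.

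**Step 2: charge only the degrees of freedom of the two covariates.** The same formula on 12 − 2 = 10 df gives 0.773. This leaves out the inflation of the standard error by chance covariate imbalance, so it is only a partial account.

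**Step 3: simulate the planned model.** The common set-up was 14 centres, mean size 17, CV about 0.99, ICC about 0.05, 40% versus 70%, no within-pair correlation, two uninformative centre-level covariates, and random effects for centre and pair. The critical value was taken from null simulations so that the test has a true 5% size. This is needed because, in run C, an uncorrected Wald z test rejected about 12% of null trials.

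| Run | Fit | Trials per scenario | Critical value of the z statistic | Power, planned model | Simpler models, same run |
|---|---|---|---|---|---|
| A | quadrature | 2,500 | 2.53–2.59 | 0.74–0.75 | not run |
| B | Laplace | 2,200 | 2.58–2.63 | 0.71–0.73 | two-level, unadjusted: 0.74–0.79 |
| C | fast approximate | 1,500 | 2.54 | 0.77 | two-level, unadjusted: 0.80 |
| D | quadrature | 2,500 | calibrated to 5% | 0.74 | two-level, unadjusted: 0.79; three-level without covariates: 0.81 |

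Monte Carlo error is about 1 point per estimate, for example √(0.74 × 0.26 / 2,500) = 0.009, before uncertainty in the critical value. Runs A to C leave out age and FIM; I cannot confirm this for run D.

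Run D separates the causes. Adding the random pair effect does not reduce power (0.79 to 0.81, within simulation error). Adding the two covariates takes it to 0.74. In run A, 40% versus 73% gave 0.82 to 0.83, so the difference detectable with 0.80 power lies between 30 and 33 points.

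**Step 4: the favourable side.**

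- Suppose pairing explains half of the between-centre variance and baseline adherence correlates 0.5 with the centre effect. Both values are assumptions; the document gives neither. The planned model then has power 0.88 (set-up of run C).
- With an ICC of 0.03, the design effect is 1.980 and the non-centrality 3.467. Even a strict paired analysis on 6 df then has power 0.82. With an ICC of 0.01 it has 0.94.

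**The case against.** **The assumptions are a planning floor.** The section presents zero correlation as a conservative setting. Pairs are matched on earlier adherence and the model adjusts for baseline-phase adherence; both are prior measures of the outcome construct, so some gain is likely. Matching would also tend to balance the two covariates between arms. The planning ICC is at least five times the pilot value. All of this stands, and it is why the shortfall is a worst case within the plan's own settings and not a forecast. It does not rescue the stated figure: 0.80 is given under those settings, and under them the planned model does not reach it.

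**A stronger reading is tempting.** A reader might infer that the arm contrast rests on seven within-pair differences, with 6 df, or 4 after the covariates. The closed form then gives 0.71 or 0.62. Those figures describe a strict paired analysis or fixed pair effects. The protocol makes the pair a random effect; when pairing explains nothing, its variance is estimated near zero and little is lost, as run D shows. Likewise, referring the planned model to a t distribution on 4 df gives 0.69 in run A, but that test has size 0.037, so 0.69 is not power at a true 5% level.

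**Error rate.** Nor does this show that the trial will use an uncorrected test. The small-sample method may be in the SAP, which is not shown.

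**Conclusion.** The concern holds in a limited form. The 0.80 belongs to an unmatched, unadjusted comparison. Under the stated ICC, cluster-size variation and zero baseline correlation, and with no gain from matching, the planned model has power of about 0.74 (0.71 to 0.77 across the four simulations) for 40% versus 70% at a true two-sided 5% level. That is 3 to 9 points below the stated figure. The main cause is adjustment for two centre-level covariates assumed uninformative with only 14 centres.

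A reader might go on to infer that the trial is underpowered. The document does not support that: with a moderate gain from matching and baseline adherence, or an ICC nearer the pilot value, power exceeds 0.80. The fault lies in the stated figure and its missing conditions. The number of centres and the choice of model are not at fault.

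**What to change.** Keep the 14 centres and the primary model. In the Abstract and the Sample size section, do one of two things:

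1. State that power for the planned analysis is about 0.74 (0.71 to 0.77) if matching and covariates explain nothing.
2. Report simulated power for the primary model at a size-controlled 5% level. State how much between-centre variance matching and baseline adherence are assumed to explain, and show the favourable case (lower ICC or informative baseline adherence) beside the worst case.

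Qualify the claim of full power in the strengths and limitations list by the same assumptions; it need not be removed.

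The cost is wording and, for the second option, a short simulation. No centres, patients or analysis steps change. The one drawback is that a published figure becomes slightly less favourable.
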